## 6.7 SAMPLE SIZE

The intention is to recruit 55 participants, allowing for a 20% drop-out rate. With 44 completers analysed there is a minimum of 90% power to detect a 1.5 µg/L effect on osteocalcin with a two-sided test at the 5% level of significance, assuming an estimate of the SD at a single timepoint of 3.0 (5). This assumes cautiously that the correlation between the repeated measurements within patients across the two periods is 0.5, whereas a previous crossover trial(6) showed a correlation of 0.8.

Following a pilot study to elucidate a reference range for osteocalcin in healthy volunteers and patients with AI, it has been shown that individuals can demonstrate reductions of up to 2.4 µg/L in the short

PRED-AID Study Statistical Analysis Plan (SAP)

term after changes in their steroid replacement regimen. It is anticipated that that larger changes in osteocalcin will be seen when patients continue on their new regimens for a longer duration.

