## 9. STATISTICAL METHODOLOGY

### 9.1 GENERAL METHODOLOGY

Data will be collected and recorded throughout the study on both paper case record files and a validated database (Oracle InForm). Following last patient last visit and all data entry final data checks will be conducted. Post the resolution of any final data queries database lock will occur for analysis.

The main analysis will be conducted following the intention-to-treat principle and include all randomised patients, according to their randomised assignment for each period, irrespective of treatment actually received. A supplementary secondary per-protocol analysis will be performed for the primary outcome.

Since randomisation is stratified by type of AI (primary vs secondary) analyses of outcomes will involve adjustment for this factor, unless otherwise indicated. For continuous outcomes, baseline values of the outcome will also be adjusted for to increase power(9). For treatment period 1 the baseline outcome will be the outcome measured at the start of period 1. For period 2 the baseline should be from the assessments measure after the completion of period 1 and washout. This baseline definition will be applied to all analyses. Change from baseline will be calculated as post-baseline value – baseline value for the associated period.

Missing baseline covariate data are not anticipated since covariates must be recorded to allocate treatment. However, if there are missing values for baseline measure of a clinical outcome, they will be replaced by the mean of the observed baseline values for all participants in all treatment arms (mean imputation). This technique improves the statistical efficiency in the estimation of treatment effect and is justifiable since randomisation ensures that baselines are independent of treatment group(10).

Every effort will be made to obtain all follow up data for all participants, including those that have stopped treatment. All available data will be included within the analysis. The primary analysis model to be employed uses maximum likelihood estimation and is consequently efficient for handling missing outcome data under a MAR assumption. Where appropriate sensitivity analyses will be conducted to check that the conclusions are robust for, example, to the missing data assumption.

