Although a washout period is incorporated into the design of the study to minimise carry-over effects, we will assess whether there is any evidence of a carry-over effect by fitting a separate linear mixed model which further includes the treatment by period interaction.

The continuous secondary outcomes will be analysed using the same modelling approach as specified for the primary outcome.

PRED-AID Study Statistical Analysis Plan (SAP)

All treatment effect estimates will be reported with 95% confidence intervals. A two-sided 5% level of significance will be used to assess the primary outcome. Statistical analysis will be conducted using SPSS or Stata.

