A carryover effect is not expected; therefore, the choice of a crossover design, the evaluation of efficacy by assessment of the change from trial baseline, and the proposed analysis model is considered to be appropriate. However, we will assess whether there is any evidence of a carry-over effect by fitting a separate linear mixed model which further includes the treatment by period interaction. In the case that there is a significant carry over effect we will fit a repeated measures linear mixed effect model using change from baseline in treatment period 1 (at 30 days and 120 days) as the dependent variable, a random participant effect, fixed effect for treatment, type of AI, baseline osteocalcin, use of bone sparing agent and time point. If this repeated measured model fails to converge, treatment effects for period 1 will be estimated using separate linear regression models for each follow-up time point, which include fixed effects for treatment, type of AI (primary vs secondary), baseline osteocalcin and use of a bone sparing agent.

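### SAP 9.5 follows a significant carry-over test with a period-1-only model and does not say which result is primary; if the period-1 result is, the type I error exceeds the stated 5%

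*Combined protocol and SAP*

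**What the plan says.** The primary analysis in SAP 9.5 is a repeated measures mixed model over both periods, and the main conclusion is tied to its treatment effect at Day 120. SAP 9.1 and 9.5 both add a check for carry-over by "fitting a separate linear mixed model which further includes the treatment by period interaction".

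SAP 9.5 then goes further: "significant carry over effect we will fit a repeated measures linear mixed effect model using change from baseline in treatment period 1". That period-1 model is adjusted for type of AI, baseline osteocalcin, use of a bone sparing agent and time point, and it has its own fallback if it does not converge. It is not listed under sensitivity analysis (9.8) or supplementary analysis (9.9).

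Three things are not stated: the significance level of the carry-over test, whether the period-1 result replaces the two-period result, and the power of the period-1 comparison. Section 9 of the protocol assesses carry-over in the same way but has no period-1 model.

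The sample size (SAP 6.7, repeated in the protocol) covers the two-period comparison only: "With 44 completers analysed there is a minimum of 90% power to detect a 1.5 µg/L effect on osteocalcin". The SD behind this figure is 3.0, and the level is 5%, two-sided.

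**The concern.** Testing for carry-over and then choosing the estimator is the classical two-stage crossover procedure. Its weakness is that the two stages are not independent. The carry-over test compares the two sequences on the sum of each patient's two period values. The period-1 comparison compares the same sequences on the first of those values. A chance imbalance between sequences in period 1 therefore tends both to trigger the switch and to make the period-1 result look significant, yet that result would still be judged at 5%.

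The test is also a between-patient comparison in a trial sized for a within-patient one, so it has little ability to find real carry-over. At stake is whether the stated 5% level applies to the result the trial will report. If the switch is triggered, there would be two Day 120 estimates and no written rule for choosing between them.

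**Working it through.** **Inputs from SAP 6.7.** 44 completers, difference 1.5 µg/L, SD 3.0, two-sided 5%, and for the correlation: "This assumes cautiously that the correlation between the repeated measurements within patients across the two periods is 0.5". A cross-period correlation of 0.8 is quoted there from a previous crossover trial. The protocol (section 3) allocates equally to the two orders, so 22 per sequence among completers.

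**Assumptions.** Carry-over test at 5% or 10%. Baseline to Day 120 correlation 0.5 or 0.8, borrowing the plan's cross-period values.

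**Step 1: the plan's own figure.** SD of the within-patient difference = 3.0 × √(2 × (1 − 0.5)) = 3.0. SE = 3.0/√44 = 0.452, and 1.5/0.452 = 3.32. Power from the noncentral t is 90.0%. 44/0.8 = 55. The stated figures reproduce.

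**Step 2: type I error if the period-1 result replaces the main one.** Let r be the cross-period correlation of the analysed outcome. The carry-over statistic uses Y1 + Y2 and the period-1 statistic uses Y1, so

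correlation of the two tests = (1 + r)/√(2(1 + r)) = √((1 + r)/2).

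The two-period treatment test uses Y1 − Y2 and is independent of the sum. Hence, with carry-over tested at level a,

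overall type I error = a × P(period 1 significant given switch) + (1 − a) × 0.05.

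The conditional probability comes from the bivariate normal distribution. For raw Day 120 values r is 0.5 or 0.8. For change from baseline it can be much lower: if both baselines and both Day 120 values all correlate at 0.5, the changes correlate at 0.5 − 0.5 − 0.5 + 0.5 = 0.

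| a | r | correlation of tests | falsely significant given switch | overall type I error |
|---|---|---|---|---|
| 5% | 0 | 0.707 | 34% | 6.4% |
| 5% | 0.5 | 0.866 | 53% | 7.4% |
| 5% | 0.8 | 0.949 | 70% | 8.3% |
| 10% | 0 | 0.707 | 25% | 7.0% |
| 10% | 0.5 | 0.866 | 37% | 8.2% |
| 10% | 0.8 | 0.949 | 46% | 9.1% |

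Example (a = 5%, r = 0.5): 0.05 × 0.533 + 0.95 × 0.05 = 0.0741.

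A simulation of a Day 120 mixed model with a random participant effect and period-specific baselines (44 patients, 15,000 trials per setting) gave 6.5-6.8% with the test at 5% and 6.7-7.6% at 10%. The excess is smaller with baseline adjustment but is present throughout.

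**Step 3: power of the carry-over test.** The between-sequence difference in patient sums has SE = 3.0 × √(2 × (1 + 0.5)) × √(2/22) = 5.196 × 0.3015 = 1.567. This uses unadjusted values at r = 0.5. For a carry-over difference of 0.75 µg/L the noncentrality is 0.75/1.567 = 0.48, and power at the 5% level is 7.5%. For 1.5 µg/L it is 0.96, and power is about 15%.

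**Step 4: power within the switched branch for 1.5 µg/L.** SE = SD × √(1/n1 + 1/n2), where the adjusted SD = 3.0 × √(1 − ρ²) and ρ is the baseline to Day 120 correlation.

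| patients per arm | unadjusted (SD 3.0) | ρ = 0.5 (SD 2.60) | ρ = 0.8 (SD 1.80) |
|---|---|---|---|
| 22 and 22 | 37% | 46% | 77% |
| 27 and 28 (all 55 give period-1 data) | 44% | 56% | 86% |

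**Step 5: overall power.** In the same simulation, with all correlations 0.5 and no carry-over, the switch occurred in about 5% of trials and overall power moved from 84.6% to 82.8%. The starting value is for the simulated model with period-specific baselines, so it differs from the 90% in step 1; only the change matters here.

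**The case against.** The strongest reply is that replacement is inferred. SAP 9.5 says only that a period-1 model will be fitted. It ties the main conclusion to Day 120 within the two-period analysis, and the protocol has no switch at all. If the period-1 model is a sensitivity analysis, the primary test keeps its 5% level. This stands in part: the documents do not say that period 2 is discarded. But they do not say the opposite either. The model is triggered inside the primary analysis section, has its own convergence fallback, and is not listed among the sensitivity or supplementary analyses. Replacement is the natural reading, and the silence is itself the defect.

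A reader might also infer that the procedure leaves under half the planned power. That would be 45%, and it holds only for unadjusted analyses (37% with 22 per arm, 44% with 27 and 28). The model specified in 9.5 adjusts for baseline, which gives 46-77% with 22 per arm and 56-86% if all 55 contribute. The loss is also confined to the switched branch.

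A reader might further infer that 9.1 and 9.5 contradict each other on the baseline and that the period-2 Day 1 value biases the estimate. Section 9.1 is explicit: "For period 2 the baseline should be from the assessments measure after the completion of period 1 and washout", and it applies that definition to all analyses. The phrase in 9.5, "the evaluation of efficacy by assessment of the change from trial baseline", is loose wording in a sentence of justification. Any bias figure would need an assumed residual effect after washout, for which the documents give no value. Nor do they show that Visit 1 precedes randomisation, so they do not support using it as the baseline for both periods.

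**Conclusion.** The concern holds as a conditional statement. If a significant carry-over test hands the conclusion to the period-1 model, the overall type I error is above the stated 5% in every setting examined: about 6.4-8.3% with the test at 5%, or 7.0-9.1% at 10%. Most of the excess comes from the switched trials, where about 25-70% are falsely significant. The size depends on the unstated level of the carry-over test and on the cross-period correlation of the analysed outcome; baseline adjustment puts it towards the lower end. If the period-1 model is only a sensitivity analysis, the 5% level stands and the defect is the missing statement.

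The rule buys little in return, since it would miss a real carry-over of 0.75 µg/L more than nine times in ten when tested at 5%. The documents do not support a claim that the trial as a whole is underpowered because of this rule.

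**What to change.** In SAP 9.5, before unblinding, state that the two-period mixed model is the sole primary analysis whatever the interaction test shows. Report the interaction estimate with its 95% confidence interval, and the period-1 estimate, as descriptive or sensitivity results, and say that neither changes the primary conclusion.

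The cost is SAP wording only. The downside is that, if real carry-over exists, the primary estimate is not switched away from it. For unadjusted Day 120 values a carry-over difference of 0.75 µg/L would shift the two-period estimate by half of that, 0.75/2 = 0.375 µg/L. The present rule would seldom prevent this, because the test would seldom detect it.

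Separately, as an editorial point, align the reference to the trial baseline in 9.5 with the period-specific definition in 9.1.

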#### **9.6 SECONDARY EFFICACY ANALYSIS**

##### **9.6.1 OTHER MARKERS OF BONE HEALTH**

## PRED-AID Study Statistical Analysis Plan (SAP)

**Outcome definition:** Treatment arm difference in i) P1NP, ii) BALP, iii) Corrected calcium, iv) PTH, v) Vitamin D, vi) NTX from baseline to Day 120.

**Analysis:** A multilevel repeated measures linear mixed effect model will be used to estimate the treatment arm difference for each of the above bone markers from baseline to Day 120. Similar to the primary analysis model, the model will include fixed effects for time (2 categories: Day 30 and Day 120), treatment arm (2 categories: prednisolone and hydrocortisone), period, type of AI (primary or secondary), baseline outcome, use of a bone sparing agent. A random participant effect will be included and an unstructured covariance matrix will be used. The treatment effect at 120 days will be reported with a 95% confidence interval. The models assumptions about random effects distributions, correlation structure and residuals will all be investigated. If any assumptions are poorly met then log transformation of the analyte in question, will be explored. If the mixed effect model including both 30 and 120 day outcomes fails to converge, treatment effects will be estimated using separate mixed linear regression models for each follow-up time point.

### 9.6.2 SURROGATE MARKERS AND RISK FACTORS FOR CARDIOVASCULAR DISEASE

**Outcome definition:** Treatment arm difference in i) Blood pressure, ii) Heart rate, iii) BMI, iv) Weight, v) Waist-hip circumference ratio, vi) NTX, vii) hs-CRP viii) Troponin I, ix) lipid profile, x)BNP; from baseline to Day 120.

**Analysis:** A multilevel repeated measures linear mixed effect model will be used to estimate the treatment arm difference in the above cardiovascular risk factors, from baseline to Day 120. Similar to the primary analysis model, the model will include fixed effects for time (2 categories: Day 30 and Day 120), treatment arm (2 categories: prednisolone and hydrocortisone), period, type of AI (primary or secondary), baseline outcome, use of a bone sparing agent. A random participant effect will be included and an unstructured covariance matrix will be used. The treatment effect at 120 days will be reported with a 95% confidence interval. The models assumptions about random effects distributions, correlation structure and residuals will all be investigated. If any assumptions are poorly met then log transformation of the analyte in question, will be explored. If the mixed effect model including both 30 and 120 day outcomes fails to converge, treatment effects will be estimated using separate mixed linear regression models for each follow-up time point.

### 9.6.3 GLYCAEMIC CONTROL

**Outcome definition:** Treatment arm difference in i) HbA1c, ii) Fructosamine, iii) fasting glucose levels, iv) insulin resistance (calculated using HOMA-IR); from baseline to Day 120.

**Analysis:** A multilevel repeated measures linear mixed effect model will be used to estimate the treatment arm difference in the above glycaemic control markers, from baseline to Day 120. Similar to the primary analysis model, the model will include fixed effects for time (2 categories: Day 30 and Day 120), treatment arm (2 categories: prednisolone and hydrocortisone), period, type of AI (primary or secondary), baseline outcome, use of a bone sparing agent. A random participant effect will be included and an unstructured covariance matrix will be used. The treatment effect at 120 days will be reported with a 95% confidence interval. The models assumptions about random effects distributions, correlation structure and residuals will all be investigated. If any assumptions are poorly met then log transformation of the analyte in question, will be explored. If the mixed effect model

PRED-AID Study Statistical Analysis Plan (SAP)

including both 30 and 120 day outcomes fails to converge, treatment effects will be estimated using separate mixed linear regression models for each follow-up time point.

#### 9.6.4 INFECTION RATES AND SEVERITY

**Outcome definition:** Treatment arm difference in the frequency of infections from baseline to Day 120.

**Analysis:** The GNCQ is a validated questionnaire that records the frequency of 6 different type of infections in the last 6 months (upper respiratory tract, lower respiratory tract, gastroenteritis, mucosal infections, lower urinary tract infections and flu). Respondents record either 0, 1, 2, 3, >3, or unknown frequencies of each type of infection.

The data will be tabulated and reported for each infection type at baseline and Day 120 for each treatment arm. McNemar-Bowkers test will be used to assess the change between treatment periods.

The data will also be weighted as follows: 0 or "don't know" will be scored as 0.5, 1-2 as 2, 3 or more as 4. The sum of the weighted scores will be treated as a continuous variable and a multilevel repeated measures linear mixed effect model will be used to estimate the treatment arm difference, from baseline to Day 120. Similar to the primary analysis model, the model will include fixed effects for time (2 categories: Day 30 and Day 120), treatment arm (2 categories: prednisolone and hydrocortisone), period, type of AI (primary or secondary), baseline weighted GNCQ, use of a bone sparing agent. A random participant effect will be included and an unstructured covariance matrix will be used. The treatment effect at 120 days will be reported with a 95% confidence interval. The models assumptions about random effects distributions, correlation structure and residuals will all be investigated. If any assumptions are poorly met then log transformation of the analyte in question, will be explored. If the mixed effect model including both 30 and 120 day outcomes fails to converge, treatment effects will be estimated using separate mixed linear regression models for each follow-up time point.

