### 3. STUDY DESIGN

Patients with stably treated primary or secondary hypoadrenalism on either hydrocortisone or prednisolone replacement will be recruited to this study from patients attending endocrinology clinics in the UK.

This study will be a phase 3, two-period, randomised cross-over, double-blind study with two treatment arms:

A) Participants given once daily low dose prednisolone (at 2-5 mg, determined by the serum level of prednisolone at 8 hours after a test dose) with placebo tablets at lunch and in the afternoon for four months (first period); followed by hydrocortisone once daily, or multiple doses daily (at their stable therapeutic regimen or the dose identified post-screening) for four months in the second period

B) Participants given hydrocortisone once times daily, or multiple doses daily (at their stable therapeutic regimen or the dose identified post-screening) for four months (first period); followed by given once daily low dose prednisolone (at 2-5 mg, determined by the serum level of prednisolone at 8 hours after a test dose) with placebo tablets at lunch and in the afternoon for four months in the second period

Participants will be randomly assigned to begin with either treatment arm. Each treatment period will be continued for 4 consecutive months. Participants will then undergo a washout period during which they will be returned to their baseline treatment for a minimum period of 2 weeks, before starting on the alternate treatment arm. The aim is to assess the effect of each treatment arm on bone health, surrogate markers of cardiovascular risk, glycaemic control, infection rates, immunology profiles, patient wellbeing and compliance.

Participant randomisation will be blocked to ensure that equal numbers of patients receive the treatments in the two orders. Each block will be randomised according the type of AI (primary vs secondary).

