### Study visits:

There will be 3 planned study visits, and 4 scheduled telephone consultations during each study period (total of 6 study visits and 8 telephone consults over both periods). The study visits will

be completed on Day 1 and Day 30 in the first month, and the final study visit of each treatment arm on Day 120. Telephone consultations will be on Days 8 and 15 in the first month, followed by further monthly consults on Day 60 and Day 90. Please refer to Appendix 2 for a schematic of the time and events on each study visit. The time window for completing each study visit is  $\pm 3$  days of the target date. Study visits which are completed outside of this window will require a protocol deviation form.

For each study visits, participants will be asked to attend the Clinical Research Facility at the Hammersmith Hospital at 0800h having fasted from 2200h the night before (permitting small sips of water only) and having taken their first steroid tablet of the day at least 2 hours prior. On arrival, observations including heart rate, blood pressure, weight and waist-hip circumferences will be recorded. Urine will be collected for measurement of additional bone markers. The urine will also be subjected to a pregnancy test in participants of child bearing potential. Routine safety blood tests, and immunological blood samples will be collected during each visit. Bone markers and glycaemic markers will also be measured. Participants will be asked to report any symptoms and to complete the SF-36, Addi-QoL and GNCQ questionnaires during each visit.

On the first day of each study period and during visit 1 (visit 4 in the second period), participants will take their usual baseline steroid replacement therapy. Participants will commence the blinded study medication from Day 2 until Day 120 (visit 3).

At the end of each study period, participants will be asked to return their remaining tablets, which will be used to gauge compliance.

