## 6.8 SCHEDULE OF TIME AND EVENTS

Pre-randomisation events are discussed in detail in the study protocol. The study will last 9 months for each participant. This will involve taking the first randomised treatment for 4 months in Study Period 1, followed by a 2-week washout period where patients return to their baseline therapy, and finally Study Period 2. Study Period 2 will also be a 4-month period in which the patient will take the alternative treatment to that used in Period 1.

There will be 3 planned study visits, and 4 scheduled telephone consultations during each Study Period (total of 6 study visits and 8 telephone consults over both periods). The study visits will be completed on Day 1 and Day 30 in the first month, and the final study visit of each treatment arm on Day 120. Telephone consultations will be on Days 8 and 15 in the first month, followed by further monthly consults on Day 60 and Day 90. Please refer to Appendix 1 for a schematic of the time and events on each study visit.

For each study visits, participants will be asked to attend the Clinical Research Facility at the Hammersmith Hospital at 0800h having fasted from 2200h the night before (permitting small sips of water only) and having taken their first steroid tablet of the day at least 2 hours prior. On arrival, observations including heart rate, blood pressure, weight and waist-hip circumferences will be recorded. Urine will be collected for measurement of additional bone markers. The urine will also be subjected to a pregnancy test in participants of child bearing potential. Routine safety blood tests, and immunological blood samples will be collected during each visit. Bone markers and glycaemic markers will also be measured. Participants will be asked to report any symptoms and to complete the SF-36, Addi-QoL and GNCQ questionnaires during each visit.

On the first day of each study period and during visit 1 (visit 4 in the second period), participants will take their usual baseline steroid replacement therapy. Participants will commence the blinded study medication from Day 2 until Day 120 (visit 3).

At the end of each study period, participants will be asked to return their remaining tablets, which will be used to gauge compliance.

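### The infection questionnaire looks back 6 months over 4-month periods, so every period-2 score mixes the two drugs and the Day 120 effect is biased

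*Combined protocol and SAP*

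**What the plan says.** SAP 9.6.4 states: "The GNCQ is a validated questionnaire that records the frequency of 6 different type of infections in the last 6 months". Under Protocol 8, participants are asked to "complete the SF-36, Addi-QoL and GNCQ questionnaires during each visit". SAP 6.8 has the visits "completed on Day 1 and Day 30 in the first month, and the final study visit of each treatment arm on Day 120", with blinded drug from Day 2. Period 1 is "followed by a 2-week washout period where patients return to their baseline therapy" in SAP 6.8; Protocol 3 has participants "returned to their baseline treatment for a minimum period of 2 weeks".

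On the analysis, SAP 9.6.4 sums weighted item scores and fits a mixed model like the primary one. It has Day 30 and Day 120 as time levels and the baseline weighted score as a covariate, and the Day 120 effect is the one to be reported. The primary model (SAP 9.5) takes change from baseline as its outcome. SAP 9.1 defines that baseline separately for each period: "For period 2 the baseline should be from the assessments measure after the completion of period 1 and washout".

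Unadjusted results are planned too. SAP 9.6.4 tabulates the items at baseline and Day 120 and applies a McNemar-Bowker test between treatment periods. SAP 9.4 presents secondary outcomes by arm, period and time point.

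Neither document shortens the recall window or mentions the overlap.

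**The concern.** The look-back is longer than a treatment period plus the washout. A score taken in period 2 therefore reaches into period 1, when the participant was on the other drug. This affects the outcome scores and also the period-2 Day 1 score, which is used as the baseline. SAP 9.1 argues, when it justifies mean imputation, that randomisation makes baselines independent of treatment. That does not hold for a period-2 baseline that records infections on the randomised period-1 drug.

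Infection rate and severity is a named objective of the trial. At stake are the size of the reported Day 120 effect, the reading of the raw tables and the between-period test, and the carry-over check, which could respond to overlapping recall rather than to any persisting drug effect.

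**Working it through.** The documents give no effect size or power for the infection outcome, so there is no figure of the plan's own to reproduce. The check counts the days on each drug inside the recall window at each visit.

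**Inputs**
- Recall: 6 months (SAP 9.6.4), taken as 182 days; 180 and 183 also tried.
- Blinded drug: Day 2 to Day 120 (SAP 6.8, Protocol 8), so 119 days per period and 29 days by Day 30.
- Gap between the blinded drugs: 14 washout days plus Day 1 of period 2, also on baseline therapy, so 15 days.
- Assumed, not in the documents: accurate recall, and risk proportional to days on drug.

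**Step 1: days in the window.** At period-2 Day 30, 29 + 15 + 119 = 163, which is below 182, so all of the period-1 drug time is still inside. At period-2 Day 120, 182 − 119 − 15 = 48 days of it remain.

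| Visit | Assigned drug | Other blinded drug | Baseline therapy |
|---|---|---|---|
| Period 1, Day 1 | 0 | 0 | 182 |
| Period 1, Day 30 | 29 | 0 | 153 |
| Period 1, Day 120 | 119 | 0 | 63 |
| Period 2, Day 1 | 0 | 119 | 63 |
| Period 2, Day 30 | 29 | 119 | 34 |
| Period 2, Day 120 | 119 | 48 | 15 |

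**Step 2: raw contrasts.** The crossover contrast in drug-days is (assigned − other), averaged over the two periods. Baseline-therapy days balance between the randomised sequences. The intended values are 29 and 119.
- Day 30: [29 + (29 − 119)]/2 = −30.5.
- Day 120: [119 + (119 − 48)]/2 = 95, and 95/119 = 0.80.
- Baseline: [0 + (0 − 119)]/2 = −59.5.

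**Step 3: change from the period baseline.**
- Day 30: −30.5 + 59.5 = 29.0, the intended value. The 119 other-drug days sit in both scores and cancel.
- Day 120: 95 + 59.5 = 154.5, and 154.5/119 = 1.30.

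**Step 4: baseline as a covariate with slope b** (b = 0 is raw, b = 1 is change).
- Day 30: −30.5 + 59.5b, negative only if b < 30.5/59.5 = 0.51.
- Day 120: 95 + 59.5b, correct only at b = 24/59.5 = 0.40, where Day 30 would be −30.5 + 24 = −6.5.
- Day 30 is correct only at b = 1, where Day 120 is 154.5. No slope puts both right.

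**Step 5: simulation of the planned model.** It used 60,000 patients, an unstructured covariance and treatment-by-time terms, and omitted the AI-type and bone-agent covariates. Assumed values were 0.25 or 0.6 infections per type per 6 months, frailty variance 0, 0.5 or 1, and a 50% higher rate on prednisolone. Counts and weighted scores gave 12 scenarios. The baseline slope was 0.66 to 1.00. The adjusted Day 30 effect was positive in all 12 (for counts, about 21% to 90% of the true effect). The adjusted Day 120 effect was about 5% to 25% too large for counts. The raw Day 30 contrast was negative in all 12.

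**Step 6: sensitivity.**
- Recall of 180 days: 46 other-drug days at period-2 Day 120; Day 120 contrasts 96 (raw) and 155.5 (change).
- Recall of 183 days: 49 days; 94.5 and 154.0.
- A 30-day washout, which the protocol's minimum allows, with 182-day recall: 32 days; 103 and 162.5 (162.5/119 = 1.37). Raw Day 30 stays at −30.5. The raw bias shrinks but the change-score bias grows, because the baseline still holds all 119 days.

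**Step 7: apparent carry-over.** By period, the Day 120 contrast is 119 then 71 on raw scores, and 119 then 71 + 119 = 190 on change. The treatment-by-period check would see these gaps with no true carry-over.

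**The case against.** A reader might infer that the Day 30 contrast has the wrong sign in the planned analysis. The documents do not support that. SAP 9.1 and 9.6.4 specify a period-specific baseline, and with change from that baseline the Day 30 contrast is +29 drug-days, as intended. With baseline as a covariate the reversal needs a slope below 0.51, and the simulated slopes were higher. Day 30 is also not the effect that SAP 9.6.4 names for reporting. The reversal is confined to unadjusted scores, such as the descriptive tables, where the period-2 Day 30 contrast is 29 − 119 = −90.

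A reader might also infer that the reported effect is diluted toward zero. That is true of raw scores only; as change from baseline it is inflated.

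Nor is the infection question lost. Period-1 scores contain no time on the other blinded drug, and pre-study therapy is balanced by randomisation. A carry-over check is planned, with a period-1-only fallback spelled out for the primary outcome. Adverse events are collected at visits and calls and tabulated by treatment and period. This is also one of many secondary outcomes.

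All of that stands, but it does not remove the overlap. Baseline adjustment changes the direction of the Day 120 bias rather than curing it, and the raw tables and the McNemar-Bowker comparison have no such adjustment.

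**Conclusion.** The point holds in this form: the recall window exceeds the period plus washout, every period-2 score mixes the two drugs, and the Day 120 effect is biased. With a 182-day recall and a 14-day washout the bias runs from about 20% too small on raw scores to about 30% too large as change from the period baseline. The unadjusted between-period test is contaminated as well, and the overlap can pass for carry-over.

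The drug-day figures rest on accurate recall and on risk proportional to days on drug; they do not depend on the infection rate. The simulated sizes do depend on the assumed rates. The 0.5/2/4 item weights are not linear in counts, so cancellation on the analysed score is only approximate. The change is worth making because infection is a stated objective and the remedy is cheap, but the primary conclusion is not affected.

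**What to change.** At Day 120 of each period, ask the six items for the time since Day 1 of that period. The window then holds 119 days of the assigned drug and none of the other. Analyse that Day 120 score without subtracting or adjusting for the period-2 Day 1 score, and without the Day 30 score. A screening or period-1 Day 1 score may stay as a covariate, but being constant within a participant it adds little to the within-patient contrast.

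If 6-month data are already collected, report the period-1 comparison between arms and treat the period-2 scores as descriptive. If onset dates exist for non-serious events, also analyse infections reported as adverse events by the drug taken at onset. The sponsor would need to confirm those dates: Protocol 7.3.2 names date of onset for the SAE form, and 7.3.1 does not mention it for non-serious events.

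The cost is a reworded recall stem and a revision of SAP 9.6.4. The shorter recall departs from the validated wording, and a period-1-only comparison is less precise than the crossover.
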